## Abstract

**Introduction:**

Lung cancer is commonly associated with smoking. However, if considered separately, lung cancer in never-smokers (LCINS) is the seventh most common cause of cancer-related death worldwide. Expanding the limited understanding of LCINS, especially in the UK, is crucial to improving diagnosis.

**Methods and analysis:**

We will establish a retrospective and prospective UK multicentre observational cohort comprising never-smoking (lifetime use of <100 tobacco cigarettes) adults with lung cancer using routinely available primary and secondary care electronic health records (EHRs). Demographic data including occupation and ethnicity, exposures and lung cancer outcomes will be extracted. Deep learning-based natural language processing will be used to analyse free-text data. Quantitative or qualitative data collection for information not available in EHR may be initiated in the future. Follow-up will be until death, withdrawal or end of study (5 years from study activation date). Primary outcomes will be sociodemographic characteristics, comorbidities, environmental exposures, pathways to presentation and symptoms. A feasibility pilot of 225 patients (25 participants per year both retrospectively and prospectively) will be undertaken at one hospital before extending the study to multiple sites. Patient representatives have been involved in adapting the research protocol including the recruitment process and patient-facing materials.

**Ethics and dissemination:**

National ethical approval has been obtained from Health Research Authority (HRA) (24/YH/0147). Access to patient records without explicit consent, including deceased patient records, is legally supported by the Confidentiality Advisory Group and HRA. The study is sponsored by University College London Hospital.

Data will be anonymised and analysed 2 years after the study start date and on study completion. Together with our patient representatives, we will disseminate data to the scientific and academic community and public through peer-reviewed publications, presentations at conferences, patient-facing charities and social media.

WHAT IS ALREADY KNOWN ON THIS TOPICWHAT THIS STUDY ADDSWe will undertake a feasibility pilot in a single centre before expanding nationally to ensure representativeness of our cohort and provide sufficient power to answer research questions on characteristics and outcomes of participants with LCINS.HOW THIS STUDY MIGHT AFFECT RESEARCH, PRACTICE OR POLICYEstablishing a cohort of never-smokers with lung cancer creates opportunities for raising patient-centred research questions, testing early detection algorithms, and additional prospective data collection.Improving our understanding of risk of lung cancer in people who have never smoked, for example by understanding patient pathways and symptoms, may improve clinical practice and support guideline development.Increased awareness that lung cancer can occur in people who have never smoked will support earlier diagnosis.

## Introduction

 Lung cancer causes the most cancer deaths, both worldwide and in the UK. In 2022, 2 480 675 adults were diagnosed with and 1 817 469 people died from lung cancer worldwide; in the UK, 50 700 adults were diagnosed with and 35 394 people died from lung cancer.^1^ Only 48% of adults survive more than 1 year, which is likely related to late diagnosis: 45% of all patients are diagnosed with stage IV (the worst stage) at presentation and 32% diagnosed following an emergency presentation.^2^ Adults with lung cancer also have poorer quality of life and patient experience, with 33.7% having three or more primary care consultations before being referred, a higher proportion compared with most cancers.^3^

Although commonly associated with smoking, up to 25% of lung cancer worldwide occurs in ‘never-smokers’ or people who have smoked <100 tobacco cigarettes in their lifetime.^4^ If considered separately, lung cancer in never-smokers (LCINS) is the seventh most common cause of cancer death worldwide.^4^

Adults who have never smoked may have different risk factors, symptoms, genetic mutations and outcomes. Consequently, there is limited understanding of LCINS, especially in the UK, where it has been identified as a research priority.^5^ There is likely to be an association with sociodemographic characteristics including deprivation and female sex.^6^ As per the National Cancer Equality Initiative, understanding sociodemographic differences is important in addressing inequalities and improving outcomes.^7^ Individuals who have never smoked may also experience late diagnosis and stigmatisation; both healthcare professionals and health-seeking individuals may not consider the diagnosis of lung cancer due to perceived low risk.^8^ In addition, patient representatives have questioned if never-smokers present with the same symptoms as ever-smokers. There is also a paucity of data on outcomes in this cohort, with one UK-based study of 436 never-smokers only reporting on individuals presenting early enough to undergo surgical resection with curative intent.^9^

Reduction in lung cancer mortality and morbidity is therefore likely to be best achieved by facilitating early diagnosis.^10^ While lung cancer screening pilot programmes are now underway in the UK to achieve this goal, never-smokers are excluded from these programmes and improved outcomes associated with stage shift from screening will not be seen in never-smokers.^11^ More research is required to understand how to improve early diagnosis in this cohort. Improving understanding of LCINS is a necessary first step.

## Methods and analysis

OLIVE is an observational cohort study which will collect data retrospectively and prospectively on never-smoking participants with lung cancer predominantly using data routinely available from electronic health records (EHRs). It has been registered with clinicaltrials.gov (NCT06575439). The study will be initiated as a pilot in one hospital in North London (University College London Hospital (UCLH)), to understand the feasibility of data collection, including completeness of data items in EHR, and linkage. External funding will be sought to subsequently expand the study across multiple sites nationally to ensure representativeness of data. This study has been externally peer reviewed and adapted following feedback from an independent multidisciplinary committee including clinicians and patient representatives organised by the National Cancer Research Institute.

### Primary objectives

To establish a data lake of never-smokers with lung cancer to:

Describe characteristics of never-smokers with lung cancer including sociodemographic characteristics, comorbidities and environmental exposures.Describe pathways to presentation and symptoms.

### Secondary objectives

Describe lung cancer outcomes such as stage at diagnosis, treatment and survival.Quantitatively or qualitatively measure the association of modifiable and non-modifiable factors that may be associated with LCINS including environmental measures, blood tests and genomic data.

### Inclusion criteria

Radiological or histological diagnosis of primary lung cancer.Smoked <100 tobacco cigarettes in their lifetime.Age over 18 years.

### Exclusion criteria

Received a prescription for nicotine replacement therapy.For prospective recruitment, unable to consent at time of study entry.

### Recruitment of participants and consent

Participant recruitment is summarised in figure 1.

**Figure 1 F1:**
[figure not shown]
Participant recruitment process.

The study start/activation date is defined as the date the study goes live at UCLH.

Potential participants diagnosed after the study activation date at each site will be identified by a member of the clinical team during lung cancer multidisciplinary team meetings, clinics and via prescription lists for systemic therapy. Potential participants will be provided a patient information sheet (PIS) which will include contact details of a research team member. A research team member will contact them at least 24 hours later and provide an opportunity to ask any questions about the study. Participants may choose to speak either face-to-face or over the telephone. Non-English speakers will be spoken to with a translation service to ensure full understanding. If they consent, they will be asked to sign the consent form electronically or on paper. The consent process including PIS and consent form (online supplemental appendix 1) has been reviewed and modified by a team of patient representatives and the information provided was deemed to be ‘concise’, ‘extensive’ and ‘clear’.

National Lung Cancer Audit data suggest that 60% of patients diagnosed with lung cancer would have died at 1 year.^2^ Due to this high mortality rate, retrospective consent is unlikely to be feasible for all participants diagnosed before the study starts at each site. Participants diagnosed before the study activation date will therefore be identified from EHR and, unless part of National Data Opt Out, will be included in our research database. Two members of the research team will independently confirm never-smoking status by reviewing EHR and free-text clinical notes. This was discussed with patient representatives who felt this was acceptable and provided suggestions on how to increase awareness. A local opt-out option will be provided by displaying posters in clinical areas and by broadcasting on each site’s website, social media and patient portals. We have received legal approval from the confidentiality advisory group (CAG) and the Health Research Authority for this retrospective recruitment.

Participants will be followed up until death, withdrawal from the study or until the end of the study (5 years from study activation date at UCLH). Those who lose capacity will have ongoing EHR review but will not be invited for any extra data collection. This was discussed with patient representatives and thought to be ‘completely acceptable’ and is explained in our PIS.

### Data collection

Data will be collected on characteristics of never-smokers with lung cancer. Data to be collected were initially determined by a systematic review,^12^ with further variables included after feedback from patient representatives and experts in respiratory medicine and oncology. Data extraction will be trialled on 100 patients to review feasibility before finalising variables that will be collected.

Routinely collected data from primary and secondary care electronic health systems will include demographic data such as sex, occupation and ethnicity, comorbidities and cancer data and outcomes. Postcode at the time of data collection will be used to determine indices of deprivation and exposure to pollution. Investigations documented in EHR including blood tests, diagnostic imaging and cancer somatic data will be reviewed. Both primary and secondary care electronic notes will be reviewed to extract and analyse free-text data and data which are not otherwise coded such as symptoms leading to presentation. There will be opportunities for machine-learning based data analysis including natural language processing. In the future, further qualitative or quantitative data collection may be initiated for information not routinely available in EHR such as blood tests and pollution measurements.

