### Sample size

It is estimated that our local hospital sees 400 patients with lung cancer each year. Between 10% and 20% (40–80) of these patients will be never-smokers. We believe it is feasible to recruit 25 participants per year both retrospectively (from 1 January 2019 to 2024 inclusive) and prospectively (from study start date in 2024 to 2029 inclusive), with an overall recruitment target of 225 participants. This will allow us to review feasibility of data collection and planned statistical analysis. We will then seek funding to expand the study across multiple sites to ensure sufficient power for data analysis. We will aim to choose appropriate sites across the UK to ensure the representativeness of the cohort.

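### Deprivation and pollution exposure are taken from the postcode at data collection, so primary-outcome variables are dated after diagnosis, with a lag that depends on recruitment group and survival

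*Protocol article*

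**What the plan says.** The Data collection section sets one rule for the whole cohort: "Postcode at the time of data collection will be used to determine indices of deprivation and exposure to pollution". It does not date data collection relative to diagnosis, consent or activation, for either recruitment group. The article nowhere mentions a postcode at diagnosis, a residential history or an exposure window.

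The variables concerned are primary. The abstract says "Primary outcomes will be sociodemographic characteristics, comorbidities, environmental exposures, pathways to presentation and symptoms", and the first primary objective is "Describe characteristics of never-smokers with lung cancer including sociodemographic characteristics, comorbidities and environmental exposures". Deprivation is a sociodemographic characteristic and pollution an environmental exposure. The Data analysis section also names exposures among the variables that may enter Cox models of one-year and five-year survival.

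The Sample size section plans recruitment "retrospectively (from 1 January 2019 to 2024 inclusive") and "prospectively (from study start date in 2024 to 2029 inclusive"). On identification, the recruitment section says "Participants diagnosed before the study activation date will therefore be identified from EHR". For the prospective group it says "Potential participants diagnosed after the study activation date at each site will be identified by a member of the clinical team". Follow-up runs until death, withdrawal or "until the end of the study (5 years from study activation date at UCLH"). Under Ethics and dissemination, analyses are set at two years after the start and at completion.

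**The concern.** The rule fixes a time point, and that point lies after the disease has been diagnosed. An address held after diagnosis may not be where the patient lived when the cancer developed or when they presented. For a primary outcome meant to characterise people with the disease, the intended value is the one at or before diagnosis.

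The gap between diagnosis and the recorded address is also uneven. It varies with recruitment route, because retrospective cases are collected after activation whatever their diagnosis date. It varies with survival too, because a survivor's address keeps updating while that of a patient who has died stops. One column of the dataset would thus carry exposure times of different meaning. If exposures enter a survival model timed from diagnosis, the covariate is measured after time zero and its error is related to the outcome, so the resulting bias need not be towards the null.

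**Working it through.** The article gives no lag or misclassification figure, so there is none to reproduce. The check has two parts.

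**1. Lag from the article's own dates**

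Inputs:
- Earliest retrospective diagnosis: 1 January 2019 (Sample size).
- Activation: some day in 2024. The day is not given, so 1 January to 31 December is used as the range.
- Possible collection times: activation, the two-year analysis, and study end at five years.

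Formula: lag = collection date − diagnosis date.

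| Collected at | Retrospective, maximum lag (patient alive) | Prospective, maximum lag |
|---|---|---|
| Activation (retrospective) or consent (prospective) | 5.0–6.0 years | near 0 |
| Activation + 2 years | 7.0–8.0 years | 2 years |
| Study end (+ 5 years) | 10.0–11.0 years | 5 years |

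These are maxima. With diagnoses spread evenly and all patients alive, the mean retrospective lag at activation is half the window: 2.5–3.0 years. For a patient who has died, no address postdates death, so the lag is at most the survival time.

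**2. Share with a changed postcode**

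Assumption, not in the documents: a fraction *a* of patients moves each year, with *a* = 5% to 10%.

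For a patient alive throughout a lag of *t* years, share changed = 1 − (1 − *a*)^*t*. At *t* = 5:
- *a* = 5%: 1 − 0.95^5 = 22.6%
- *a* = 10%: 1 − 0.90^5 = 41.0%

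These figures apply only to people who live the full five years. For all retrospective cases, moves must stop at death. The article gives two one-year figures for lung cancer as a whole: 60% dead at one year (recruitment section), so 40% alive, and 48% surviving more than one year (Introduction). Assume exponential survival with hazard λ = −ln(S₁), and a moving rate m = −ln(1 − *a*). Then

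share changed by *t* = [m / (m + λ)] × [1 − exp(−(m + λ)*t*)].

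Here λ = 0.916 for 40% and 0.734 for 48%; m = 0.0513 for 5% and 0.1054 for 10%. At *t* = 5:

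| One-year survival | *a* = 5% | *a* = 10% |
|---|---|---|
| 40% | 0.0530 × 0.992 = 5.3% | 0.1031 × 0.994 = 10.3% |
| 48% | 0.0653 × 0.980 = 6.4% | 0.1255 × 0.985 = 12.4% |

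Across the retrospective group at a five-year lag, about 5–12% would have a changed postcode. If *a* were 2%, the five-year survivor figure would be 1 − 0.98^5 = 9.6%.

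The difference between the two sets of figures matters in itself. At most 5–10% of those dying within a year would have a changed postcode, against 23–41% of five-year survivors. The error therefore rises with survival.

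With the postcode taken at diagnosis, the lag is zero in both groups by definition. No sample size, power or significance level changes.

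**The case against.** Several points on the other side have force.

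- **Scope.** A reader might infer that the problem is confined to retrospective participants and that the prospective ones are close to error-free. The article does not support this. One rule covers everyone, prospective patients are also approached after diagnosis, and the collection time is undated. Only lags above five years are confined to the retrospective group. These are also recruitment groups of a single cohort, not arms, and no comparison between them is specified.
- **Size.** A reader might apply 23–41% to the whole retrospective group. That treats every patient as alive for the full lag, against the article's own mortality figures. The average is much lower, as shown above. If never-smokers survive longer than lung cancer patients as a whole, it would be higher, but the article gives no such figure.
- **A move is not always an error.** A local move may leave the deprivation band or the pollution estimate unchanged. Nothing in the article shows how often patients move because of illness.
- **Consequence.** The primary objectives are descriptive, the Cox analysis is only a possibility, and exposures rather than deprivation are the covariates named.
- **Pilot status.** Extraction is to be tried on 100 patients before the variables are settled, which leaves room to refine the rule.

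These points reduce the size and urgency, and they stand. They do not remove the defect: the article states the time point rather than leaving it open, and nothing elsewhere corrects it.

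**Conclusion.** The point holds as a should-fix. The stated rule dates two primary-outcome variables after diagnosis, by up to 5–6 years at activation in retrospective survivors and by more if collection is later. The lag is truncated at death, and it is short in prospective participants only if collection happens near consent.

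The lags rest on the article's dates alone. The percentages in the working are illustrative upper limits on misclassified exposure, since some moves leave the value unchanged. They depend on an assumed moving rate, on exponential survival, and on one-year survival for lung cancer in general.

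The article does not support the conclusion that the survival analysis is already compromised, since that analysis is conditional. If it is run with these exposures, the survival-related error would enter it.

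**What to change.** Replace the postcode sentence with wording such as: *For every participant, deprivation index and pollution exposure will be derived from the postcode at the date of diagnosis, taken from dated hospital or GP address records.* Where no dated address exists, use the postcode at data collection, flag it, and exclude flagged cases in a sensitivity analysis. Use the 100-patient extraction trial to find out how often a dated address is available. Settle this before the data are anonymised for the two-year analysis, after which a diagnosis-date postcode may be hard to recover.

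Cost: some older records will need the fallback, and a protocol amendment may be required, since the article says amendments will be submitted for approval. The article does not show that dated addresses are held, so the share needing the fallback is unknown. A diagnosis postcode also remains a single time point: it gives a common reference date, not an exposure history, and should be reported as such.

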### Data storage

Data will be stored in UCL Data Safe Haven, a secure solution for storing, handling and analysing identifiable data. This has been certified to ISO27001 information security standard and conforms to NHS Digital’s Information Governance Toolkit. All data will be stored, processed and managed within the security of this system. Data is protected in a ‘walled garden’ and users are prevented from accessing external network resources such as email. Data will be stored for 5 years after the end of the study.

### Sample size

It is estimated that our local hospital sees 400 patients with lung cancer each year. Between 10% and 20% (40–80) of these patients will be never-smokers. We believe it is feasible to recruit 25 participants per year both retrospectively (from 1 January 2019 to 2024 inclusive) and prospectively (from study start date in 2024 to 2029 inclusive), with an overall recruitment target of 225 participants. This will allow us to review feasibility of data collection and planned statistical analysis. We will then seek funding to expand the study across multiple sites to ensure sufficient power for data analysis. We will aim to choose appropriate sites across the UK to ensure the representativeness of the cohort.

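### The recruitment target of 225 does not follow from 25 participants per year over the stated windows, which give 250–275, and the rate is not reconciled with the retrospective inclusion rule

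*Protocol article*

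**What the plan says.** The Sample size section of the protocol article gives one rate, two windows and one total. The rate and windows are "25 participants per year both retrospectively (from 1 January 2019 to 2024 inclusive) and prospectively (from study start date in 2024 to 2029 inclusive"; the sentence ends "with an overall recruitment target of 225 participants". The abstract (Methods and analysis) presents the same total as the result of the same rate: "A feasibility pilot of 225 patients (25 participants per year both retrospectively and prospectively) will be undertaken at one hospital". Both the abstract and the section on recruitment and consent place the end of the study 5 years after activation at the pilot hospital.

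On the supply of patients, the Sample size section says that "our local hospital sees 400 patients with lung cancer each year" and that "Between 10% and 20% (40–80) of these patients will be never-smokers".

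On who enters the retrospective arm, the section on recruitment and consent says that patients diagnosed before activation will be "identified from EHR and, unless part of National Data Opt Out, will be included in our research database". Two team members independently confirm never-smoking status from the records, and a local opt-out is offered. The article states no cap and no sampling step.

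**The concern.** The target is a product of a rate and a number of years, and all three are printed, so they should agree. They do not: no reading of the windows yields the number of years that 225 requires. This is the only figure for the overall size of the pilot, and it appears in both the abstract and the methods. A pilot whose purpose is to judge feasibility needs a target that matches its own rate and duration, or recruitment performance cannot be assessed against it.

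The second issue is which patients make up the retrospective arm. That arm needs no individual consent and is described as taking everyone identified who has not opted out. A rate of 25 per year is well below the 40–80 never-smokers expected each year. The primary objectives are descriptive, so whether the arm is a complete series or a part of one determines whom the reported percentages describe.

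**Working it through.** **Inputs, all from the protocol article**
- Rate: 25 per year (Sample size; abstract).
- Retrospective window: 1 January 2019 to 2024 (Sample size). It ends at activation, at some date in 2024, so it lasts 5 to 6 years.
- Prospective window: activation in 2024 to 2029 (Sample size). The study ends 5 years after activation (abstract; recruitment and consent), so it lasts 5 years.
- Stated target: 225 (Sample size; abstract).
- Supply: 400 lung cancer patients per year, 10–20% of them never-smokers, or 40–80 (Sample size).

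**Step 1: try to reproduce 225.** Years implied = 225 / 25 = 9.

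| Reading of the windows | Years | × 25 |
|---|---|---|
| Activation at the start of 2024: 5 + 5 | 10 | 250 |
| Activation in mid-2024: 5.5 + 5 | 10.5 | 262.5 |
| Activation at the end of 2024: 6 + 5 | 11 | 275 |
| Distinct calendar years 2019–2029 | 11 | 275 |
| 2024 counted in full in both windows: 6 + 6 | 12 | 300 |

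None gives 225. Splits of 5 + 4, 4 + 5 or 6 + 3 years would, but the article states none of them. The same result can be reached from the other side. Five prospective years give 5 × 25 = 125, which leaves 225 − 125 = 100, or 4 retrospective years. Yet 1 January 2019 to any date in 2024 is at least 5 years.

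**Step 2: size of the discrepancy.** 250 − 225 = 25, and 25 / 250 = 10%. 275 − 225 = 50, and 50 / 275 = 18%. The literal double count of 2024 (300) lies further away still and is not used for the range.

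**Step 3: retrospective arm under the two statements.**
- At 25 per year: 25 × 5 = 125 to 25 × 6 = 150.
- Including all never-smokers seen: 40 × 5 = 200 to 80 × 6 = 480.

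The second range is gross. It precedes the exclusion for a nicotine-replacement prescription, the National Data Opt Out, the local opt-out and any failure to confirm never-smoking status. The article gives no rate for any of these, so a net figure cannot be computed. For the two statements to meet at 25 per year, these losses together would have to remove 1 − 25/40 = 37.5% to 1 − 25/80 = 68.75% of the patients seen. The article neither states nor suggests a loss of that size.

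**The case against.** The best defence is that 25 per year is worded as what the team believes is feasible, in a descriptive pilot with no power calculation and with adequate size deferred to a multisite expansion. On that reading the figure is a cautious rate that may sit below the number available, the inclusion rule already governs the retrospective arm, and a target set too low harms nothing. Much of this stands. It lowers the severity, and it means that no direct contradiction is shown between the rate and the inclusion rule, only an unexplained gap. It does not rescue 225, which is still not 25 times any number of years in the stated windows. Nor can the difference be put down to recruitment closing before the end of follow-up, because the Sample size section itself runs prospective recruitment into 2029.

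The article is also a condensed account, and details of selection may be in the full protocol. That is fair for the sampling detail, but not for figures in a single sentence that disagree.

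A reader might infer several stronger things that the article does not support:
- **That 25 per year is a cap, so that only 31–63% of eligible patients enter.** The text does not state a cap, and these fractions (25/80 and 25/40) use the gross denominator.
- **That selection favours longer-surviving or better-documented patients.** Nothing shows this. The retrospective arm dispenses with consent because of high mortality, and it covers the records of deceased patients.
- **That the threshold for survival analysis rests on 225.** The Data analysis section assumes 100 events for 10 covariates independently of the target, makes the Cox model optional and allows for longer follow-up.
- **That 200–480 patients would actually be included.** That is a count before all losses.

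**Conclusion.** The target of 225 is inconsistent with its own inputs. With activation anywhere in 2024 and 5 years of prospective recruitment, 25 per year gives 250–275, so the stated figure is low by 25–50 participants, or 10–18%. This rests only on the printed rate and windows.

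The relation between 25 per year and the retrospective inclusion rule is unresolved: 125–150 patients on one statement, against a gross 200–480 on the other. How far apart they are after exclusions, opt-outs and confirmation of smoking status cannot be determined from the article.

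Severity is minor to moderate. The pilot is descriptive, the error understates its size, and no power claim depends on 225.

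**What to change.** 1. In the Sample size section and the abstract, make the rate, windows and total agree. Either restate the target as 250–275 (a single number once the activation date is fixed), or keep 225 and state retrospective and prospective windows that total 9 years. The article does not indicate which split was intended, so the sponsor must choose.
2. State how 25 per year relates to the retrospective inclusion rule. Either say that 25 per year is a minimum and that all consecutive eligible patients who have not opted out are taken, or, if review capacity limits the number, say that a random sample is drawn within each calendar year.

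The cost is small. The first item and the wording of the second are text corrections. Taking all eligible patients does add work, because two team members review each record: on the gross figures up to 1.6 times (40/25) to 3.2 times (80/25) the retrospective number at 25 per year. The sampling option avoids most of that, but it needs a list of candidates for each year from which to draw.
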